**Figure 1 figure1:**
[figure not shown]
Housing First for Youth randomized controlled trial study design HF: housing first; TAU: treatment-as-usual.

### Housing and Supports Services

Participants randomized to the HF intervention group receive housing and support in accordance with the HF4Y model’s framework and core principles [20,21]. The program staff were extensively trained on the intervention requirements to ensure fidelity to the model. Supports offered include the provision of a housing subsidy, such that participants spend ≤30% of their income on housing based on the private rental market. Participants may also live in social, supported, or alternative housing with no treatment preconditions (eg, in-place crisis, transitional, supportive, or scatter-site housing with mobile support), in which case the rent supplement is not required. The provision of support services is not bound by any preconditions (eg, housing readiness, sobriety, and engagement in other treatment), although participants agree to be visited in their unit a minimum of once per week by program staff for a length of time that is appropriate to their level of need.

It is important to note that although a range of housing options is available in both Ottawa and Toronto, the immediate access to specific options may vary. Factors such as demand, capacity, and funding influence the availability of each option. Resource limitations or eligibility criteria may result in some options being more readily available than others.

The intervention services young people receive within the HF4Y model, including a housing rent subsidy and a range of supports delivered via housing-based case managers, are designed to bridge the financial gap and enhance young people’s ability to secure suitable housing, such as private market rentals, which they may not be able to afford on their own. In addition, housing-based case managers provide support in navigating housing processes while ensuring that young people are aware of their housing prospects. These supports include providing young people with comprehensive information about the various housing options available in the community as well as facilitating discussions with youth on the advantages and disadvantages of each option, including any potential constraints in accessing their preferred types of housing. Through these conversations, young people actively participate in the decision-making process, enabling them to select the type of housing, neighborhood, and level of services that best align with their individual needs and preferences. This means that young people can also reassess their needs and make adjustments to their housing options as required. This approach empowers young individuals, promotes informed decision-making, and supports their personal growth and development.

The HF4Y model offers a wide array of support services related to housing retention, well-being, income and employment, education, and social inclusion as well as complementary supports such as peer support that are offered by providers who are based off-site. These support services are individualized and tailored specifically to participants’ needs, preferences, and cultural backgrounds. Adapted from the Pathways model [5], the support services are provided in the home or community, using mostly intensive case management, which is appropriate for individuals with moderate mental health needs and linked them primarily to 1 case manager rather than a team. In the HF4Y program model [20-22], an intensive case management model should be established in the range of 7 to 10 youths per case manager, with 7 being the ideal number to produce the most desired, optimal outcomes for youth. Case managers work with participants to obtain and maintain housing and to navigate referrals to external services (eg, mental health support and medical services).

Compared with the HF intervention group, no active intervention is introduced to the TAU group. However, participants may continue to access existing supports and housing available in each community, including income support, drop-ins, physical and mental health clinics, emergency shelters, transitional housing, and longer-term housing. As both Ottawa and Toronto are urban centers with agencies that deliver housing services targeted to young people, it is recognized that some individuals in the TAU group may over time, through new or existing programs, access some of the same services being offered to the HF intervention group. It is also likely that the usual care service patterns will differ between cities.

### Participant Retention

Participation retention is a major concern, particularly in RCT studies where receiving maximum response rates and compliance with the research protocol is pivotal to their success. In this longitudinal study, enrolling young people experiencing homelessness and housing precarity was a particularly difficult task because of their involvement in a variety of competing activities, such as school and meeting their basic needs. In addition, barriers such as unstable housing and frequent transitions have made it difficult for youth to maintain a consistent mode of communication over time. The COVID-19 pandemic in February 2020 compounded these challenges, as it disrupted the efforts made to establish and maintain contact with youth.

Existing literature suggests strategies to minimize participant attrition, which broadly include baseline tracking procedures such as collecting detailed information on the participant’s location and follow-up procedures, including sending reminders to conduct follow-up interviews [51-53]. Consistent with the literature, this study uses an array of techniques to maintain contact with hard-to-reach participants, which include building rapport, supplementing traditional tracking methods (eg, phone, email, social media, and known associates) with new technologies, and offering financial incentives. More importantly, as data collection is still underway, a key factor is cultivating an appreciation of the contribution of the respondents as experts. Such a “participant-centered” approach [54] ensures that participants are aware of the impact of their participation in the outcomes and success of the study, thereby increasing the likelihood that they will continue to be engaged in the study. Although the existing body of research suggests varying rates of retention depending on the types of strategies used, ranging from 65% to 85% [53], this study aims to keep approximately 75% of the participants engaged in the study over 4 years.

### Outcome Areas and Measures

Building on the existing body of research including the At Home/Chez Soi national study, primary outcomes were selected to reflect the unique characteristics of youth experiencing homelessness and to measure the effectiveness of the HF4Y program interventions that are consistent with the program’s core principles and the detailed service delivery model [20,21,55]. In evaluating complex interventions, there are a range of factors that likely have an impact on housing stabilization, including sufficient and stable income, health and well-being, involvement with the justice system, involvement in education and employment, and social inclusion [56,57]. The core primary outcomes are thus selected to assess the effectiveness of HF4Y interventions on housing stability (as defined by a joint function of the number of days housed and the number of moves), health and well-being (mental and physical health status), and access to complementary supports, with secondary outcomes consisting of participation in education and employment and social functioning, as listed in Table 1 [55]. Multimedia Appendix 1 provides a comprehensive description of the measures.

In Ottawa and Toronto, interviews and surveys designed to collect quantitative data were administered at baseline, and each follow-up takes place at specific time points (3-6 months) over 4 years. At entry into the study (baseline), youth participants were interviewed using a range of questions aimed at collecting demographic data, physical health conditions, access to care, housing retention (using residential timeline follow-back), and employment (using vocational timeline follow-back; refer to Multimedia Appendix 1 for a detailed description of the interview measures). Following the interview, the participants were administered a battery of survey measures for physical and mental health and well-being, social inclusion, self-esteem and self-efficacy, resilience, hope, quality of life, and a measure reflecting complementary skills that impact the various domains (Table 1). In-person and phone-based follow-up quantitative interviews are being conducted at 3- or 6-month intervals depending on the instrument used. Since the onset of the COVID-19 pandemic, interviews and surveys with youth participants have been conducted remotely via Zoom (Zoom Video Communications) or phone. The number and timing of interview sessions were decided based on two factors: (1) the intention to evaluate longer-term outcomes and trajectories of change for each participant and (2) the recognition that participants may miss appointments owing to the nature of their situation and issues. This may be even more pronounced in the TAU group that has no interaction with the intervention, and, therefore, a potentially weaker incentive to attend appointments as scheduled.

The collection of primary data is mostly achieved through interviews conducted via Zoom or phone, with a mixture of both paper- and computer-based survey methods. Each interview appointment takes approximately 30 to 60 minutes to complete, and the participants are compensated for their time. Computer-based surveys administered through the *Qualtrics* survey platform are entered into a secure central database using wireless technology. Hard-copy data are stored securely following double-lock procedures at each site, and electronic backups are stored on cloud-based, secure, institutional network–based storage. Several strategies are being used to ensure optimal data quality: (1) using validated and reliable tools for susceptible youth populations; (2) using a cross-site protocol for data management, data entry, quality checking, and cleaning; (3) practicing common data-checking routines at each site through monthly multisite data quality committee meetings; (4) training interviewers for face-to-face and web conferencing interaction with participants; and (5) fielding interviewer questions centrally and making decisions where necessary across both RCT sites.

Following a sequential mixed methods approach [38], a subset of 20 youths per group at each RCT site was randomly selected (10 participants from the HF intervention group and 10 from the TAU group) to participate in a narrative interview, once at 6 months and later at 18 months. Demographic data of participants successfully recruited into the qualitative study were then assessed to ensure balance in demographic variables including age, gender identity, and ethnoracial background.

The purpose of this qualitative research inquiry is (1) to supplement the quantitative data collected with respect to the effectiveness of the HF4Y program and (2) to help identify areas that need improvement for future scaling of the HF4Y program. This qualitative approach is also intended to allow us to understand the lived and living experiences of study participants in their own words through life story (or “narrative”) interviews. For the large majority of youth participants, homelessness is not the product of a single event, but it is seen as a journey in which individual agency and life decisions take center stage. The qualitative interviews follow a semistructured format and include questions that are mapped onto the quantitative outcome domains. The follow-up interviews help understand how youths’ lives have changed during the RCT and what things may have contributed to those changes. These interviews specifically inquire about the types of services within and outside the HF4Y program that participants are currently receiving. They also explore the types of services participants require but are not currently receiving as well as their perspectives on the helpfulness or limitations of the services they are accessing.

### Analytical Procedures

HF intervention and TAU groups will be compared within each RCT site; although if it is determined that no significant differences exist between the 2 sites in terms of sociodemographic characteristics and outcome measures collected at baseline, the TAU and intervention groups will be combined accordingly across sites to increase the power of the study. There will be an interim analysis using 2-year quantitative data, with the final analyses based on the 4-year data. It is expected that certain participants might not adhere to the protocol or could discontinue their involvement owing to health issues or fatigue arising from repeated assessments. As deviations from the protocol are inevitable and likely to occur in real-time practice [58-60], there exist a number of approaches that can preserve the integrity of the randomization process including an intention-to-treat analysis, which considers all participants initially randomized in the study.

In addition, certain participants may be more likely not to respond to surveys, or certain questions might be more likely to have missing responses. With respect to missing data, 3 common mechanisms can be observed: missing completely at random, missing at random, and missing not at random [61,62]. For data missing completely at random, single imputation methods can be used to address the missing values, albeit with a tendency to provide conservative estimates of the treatment effect; for example, missing values can be replaced with the last observed values or the mean values. For data missing at random and missing not at random, multiple imputation can be used, which produces a more accurate and less biased estimate of the treatment effect [63].

For continuous outcome measures, differences between the intervention and control groups will be examined by using mixed-effects modeling for repeated measures. For binary outcomes, logistic models will be used, and negative binomial modeling will be used for all count outcome measures to account for any possible overdispersion in the data. Sociodemographic characteristics collected at baseline will be entered into the models as covariates, and the interaction between time and intervention will be considered to capture the interaction effects. All quantitative analyses will be conducted in SPSS (IBM Corp) and R studio (Posit) software packages with power set at 80% (α=.05 and β=.20) to detect an effect size of 0.5 between the TAU and intervention groups for the primary outcome domains.

Qualitative data will be assessed through thematic analyses to identify common themes related to outcomes and to analyze the underlying intervention process, consistent with the approaches suggested by Miles et al [64] and Saldaña [65]. The qualitative data provide a rich source of the narratives regarding young people’s experiences with homelessness, housing instability, and interaction with the HF4Y program itself. Interviews will be transcribed and imported into NVivo (QSR International) software for analysis. Rather than focusing on preexisting theoretical constructs using an a priori method, an emergent, bottom-up approach will be used for coding [64]. The process of coding will shift back and forth from the key narratives provided by the participants to the researcher’s interpretation of the meaning of those narratives, which will be documented through the researcher’s analytic memos. Recurring patterns gleaned from the codes will be grouped as themes and will be thematically classified under broader themes. The final set of themes will be summarized and presented in a table, where representative quotes from transcripts will be paired with themes as textual evidence.

In addition to the quantitative and qualitative analyses, each agency is responsible for completing monthly reports that provide important metrics for all participating youth, including demographic information and key indicators such as the number of youth housed during the month and the number of youth who exit a program. Furthermore, program fidelity evaluations are conducted within each HF4Y program. These evaluations assess how well the intervention aligns with the HF4Y model and identify any areas that may require adjustments or additional support.

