As part of the MtS Youth Homelessness Social Innovation Lab, 3 demonstration projects on HF4Y are currently being implemented by community agencies in Ottawa, Toronto, and Hamilton in Ontario, Canada. In each of the cities, agencies that work with youth experiencing homelessness are implementing and operating the HF4Y program, consistent with the model developed by Gaetz et al [21]. Each testing site focuses on specific populations of young people experiencing homelessness. Although Ottawa focuses on youth currently experiencing homelessness, Toronto focuses on youth exiting the child welfare system as a preventive intervention.

In Hamilton, an RCT design is not being used as it does not align with the values of Indigenous knowledge and traditions. Instead, a hybrid model is being implemented; it is called *Endaayaang* and combines the core principles of HF4Y with Indigenous ways of knowing and cultural practices. In Canada, Indigenous youth include 3 distinct cultural groups, that is, First Nations, Metis, and Inuit. Youth from these communities are overrepresented in the population of youth experiencing homelessness because of the history of colonialism (including practices aimed at eradicating Indigenous cultural traditions such as residential schools and the 1960s Scoop); involvement with child protection services; and the presence of intersecting forms of oppression, intergenerational trauma, and marginalization [28-30]. The adaptation of the HF4Y program necessitates the inclusion of Indigenous leadership in the program for it to succeed. Therefore, an Indigenous-led methodology that adopts a hybrid approach combining Western and Indigenous methodologies and ways of knowing is being used [31]. This approach combines elements from the settler-developed HF4Y model with Indigenous ways of knowing and cultural practices, rooted in the understanding that Indigenous youth must experience a sense of belonging within their community and have access to cultural and spiritual guidance from Elders and Traditional Knowledge Keepers to achieve positive outcomes.

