**Social inclusion**					
	Family and natural supports	Multidimensional Screener of Perceived Social Support		6 months	
	Sense of belonging to the community	Psychological Community Integration Scale [49]		6 months	
	Engagement in cultural and meaningful activities	Physical Community Integration Scale [50]		6 months	

^a^Primary outcomes domains.

^b^The residential timeline follow-back (RTLFB) is designed to assess various aspects of housing status and stability. In this study, it serves to incorporate point-in-time assessments and longitudinal evaluations of participants’ housing stays and transitions. It allows building a chronological record of each respondent's residential history between successive interviews. In addition, the RTLFB collects information about the type of residence, the individuals the participants are living with, and the reasons for moving in and moving out during the specified period. The records obtained from the RTLFB will be analyzed to gain insights into the specific places where young people stayed during the study, as well as the reasons for their moves in and out of different residences. This information will contribute to a comprehensive assessment of the effectiveness and impact of the HF4Y intervention on their housing stability and overall well-being.

^c^The measures and intervals listed will be used at the interval indicated to collect data over 48 months (eg, the residential timeline follow-back is being used every 3 months for 48 months).

^d^VTLFB: vocational timeline follow-back.

It was expected that baseline differences would exist across sites, reflecting the diverse demographic, socioeconomic, and ethnoracial background of participants based on regional characteristics. To achieve representativeness in the RCT sample, homogeneous sampling was used [38], which targeted several shared characteristics including age range (youth aged 16-24 years) and those who were experiencing homelessness or were at risk of homelessness. For each site, a minimum of 63 participants needed to be recruited for the study to be able to detect an effect size of 0.5 between the TAU group and the intervention group for the primary outcome domains, given α=.05 and β=.20. However, the total number of participants recruited was 148 to account for an attrition rate of 25%, following similar RCT-designed studies [11,17].

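### Sites are pooled only if baseline tests find no significant site differences: the wrong criterion, one the plan itself expects to fail, and it sets aside the analysis closest to the stated 80% power

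*Protocol article*

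**What the plan says.** Under Analytical Procedures, comparison of the arms within each site is the default. The exception applies "if it is determined that no significant differences exist between the 2 sites in terms of sociodemographic characteristics and outcome measures collected at baseline"; in that case "the TAU and intervention groups will be combined accordingly across sites to increase the power of the study".

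Three other places bear on whether that condition can be met:

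- Data Collection and Randomization (text after Table 1): "It was expected that baseline differences would exist across sites, reflecting the diverse demographic, socioeconomic, and ethnoracial background of participants".
- Making the Shift Youth Homelessness Social Innovation Lab: "Although Ottawa focuses on youth currently experiencing homelessness, Toronto focuses on youth exiting the child welfare system as a preventive intervention".
- Participants' Recruitment: Ottawa took homeless youth aged 18 to 24. Toronto took youth aged 17 to 24 with a child welfare history, including some only at risk of homelessness. The main referral routes also differ.

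On size, Data Collection and Randomization states: "For each site, a minimum of 63 participants needed to be recruited for the study to be able to detect an effect size of 0.5", "given α=.05 and β=.20". Analytical Procedures repeats 80% power "to detect an effect size of 0.5 between the TAU and intervention groups for the primary outcome domains".

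**The concern.** There are three problems with the rule as written.

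1. **The plan expects its own condition to fail.** Child welfare history is close to an entry criterion at one site only, and baseline housing status differs because of whom each site recruits.
2. **The condition does not address the question that pooling raises.** Baseline differences between sites describe who was enrolled where. They do not make the arms within a site unlike each other. The relevant question is whether the effect of the intervention differs by site, and the rule does not ask it.
3. **A non-significant test is read as similarity.** With 86 and 62 participants, a moderate real difference can pass unnoticed, while one chance finding among many tests can block pooling.

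At stake is the main comparison. If the condition fails, the trial reports two separate site comparisons, each with less power than the combined one.

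**Working it through.** **Inputs.** Effect size 0.5 SD, α = .05, power 80%, attrition 25% (Data Collection and Randomization; Analytical Procedures; Participant Retention gives the matching 75% target). Allocation: Ottawa 44 intervention and 42 TAU; Toronto 31 and 31; combined 75 and 73 (148). Two-sided testing is assumed, because the article does not state sidedness.

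**Step 1. The plan's own figure.** The usual formula per arm is n = 2(z₀.₉₇₅ + z₀.₈₀)²/d² = 2(1.960 + 0.842)²/0.25 = 62.8, so 63 per arm, or 126 per comparison. The stated 63 is thus reproduced as a number per arm, not as a total per site. A site total of 63 (31.5 per arm) gives about 50% power.

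**Step 2. Power at d = 0.5** (two-sample t test, noncentral t):

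| Comparison | Full retention | After 25% loss |
|---|---|---|
| Combined, 75 v 73 | 86% | 74% (111 left) |
| Ottawa, 44 v 42 | 63% | 51% (64.5 left) |
| Toronto, 31 v 31 | 49% | 39% (46.5 left) |

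Full 80% power after 25% loss would need 126/0.75 = 168 randomised, against 148.

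**Step 3. Does keeping site in the analysis cost power?** The information about the arm difference, in units of 1/variance with SD = 1, is:

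- stratified by site: 1/(1/42 + 1/44) + 1/(1/31 + 1/31) = 21.49 + 15.50 = 36.99
- unstratified: 1/(1/73 + 1/75) = 36.99

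Stratifying costs essentially nothing.

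**Step 4. How often would the condition block pooling if the sites did not differ at all?** The article does not say how many variables are tested, or that each is tested separately at .05; both are assumed here. Table 1 has 20 rows. Dropping the life skills instrument that appears twice and the educational achievement item with a 24-month interval leaves about 18. Adding five sociodemographic variables to all 20 gives 25. The chance of at least one significant result is:

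| Tests | Independent, 1 − 0.95^k | Pairwise correlation 0.3 (simulated) | Correlation 0.5 (simulated) |
|---|---|---|---|
| 18 | 60% | 51% | 40% |
| 25 | 72% | 61% | 47% |

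**Step 5. And if they do differ?** A true site difference of 0.5 SD on one measure (86 v 62) is flagged 85% of the time, and one of 0.3 SD 44% of the time. As an illustration, if 3 of 20 independent measures truly differ by 0.3 SD, pooling survives with probability (1 − 0.437)³ × 0.95¹⁷ = 7.5%.

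**The case against.** **The populations differ by design, so a within-site default is coherent.** This is fair as far as it goes. Population, eligibility and usual care differ between the cities and may modify the effect, and one stated objective concerns subpopulations. It is a good reason to report each site's estimate and the interaction. It does not support deciding on pooling by baseline significance tests, which say nothing about effect modification.

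**The plan sizes each site at 63, so each site stands on its own.** It does not, because 63 is the number per arm (Step 1). Even on the plan's terms, Toronto's 62 falls one short before attrition.

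**The power figures ignore the planned repeated-measures models.** This stands as a limit on the figures. If the correlation between measurements were 0.4 to 0.6 (assumed), adjusting a single endpoint for baseline after 25% loss would give Ottawa 58% to 70%, Toronto 44% to 55% and the combined analysis 81% to 90%. If the primary contrast were the baseline-adjusted mean of eight follow-ups and the effect on that mean were still 0.5 SD, Ottawa would reach 94% to 96%, Toronto 84% to 87% and the combined analysis over 99%. The article gives no correlation and does not say which contrast is primary. The figures in Step 2 are therefore a simple benchmark at the pessimistic end, but the ordering of the three analyses does not change.

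**Readings that go too far.** A reader might infer any of the following:

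- That pooling is the only adequately sized analysis. It also misses 80% after planned loss on the simple calculation.
- That the pooled model would omit site. The article is silent, and model terms are commonly left to a fuller document.
- That site differences are irrelevant. They matter for interpretation, though not for the validity of a stratified comparison.
- That the rule inflates Type I error. It uses baseline data compared between sites, not arm differences in outcome, and no inflation has been shown.

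The article also does not say whether the randomisation sequence was stratified by site. The argument does not need it: under simple randomisation, arms compared within a site are still randomised groups.

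**Conclusion.** The point holds. The article states a pooling rule that rests on the wrong criterion and that its own text leads one to expect will fail. That expectation rests mainly on the stated differences in population and recruitment; the false-blocking rates support it but depend on an assumed number of tests and on independence.

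On the simple two-sample benchmark, following the rule replaces one comparison with 86% power (74% after planned loss) by two with 63% and 49% (51% and 39% after loss). Pooling is the analysis closest to the stated 80%; it does not meet it at the planned attrition. The absolute figures would rise with any gain from baseline or repeated measures, which the document does not quantify.

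**What to change.** Delete the baseline-similarity condition. State that the primary analysis combines both sites, with site as a stratum or fixed effect, whatever the baseline comparison shows. Report the arm-by-site interaction and the site-specific estimates with confidence intervals as secondary analyses, since the populations differ by design. Describe baseline characteristics by site without testing them as a gate.

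Date the change and record its reason. The Results section says analysis of data to 24 months is under way, so readers need to see that the choice did not follow from the findings.

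The cost is a few sentences and no new data. The small downside is that the headline result averages over two populations; the interaction and the site estimates make that visible. The statement of 63 participants per site needs its own correction and should not be used to justify separate site analyses.

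### The article misstates what its missing-data methods do: single imputation is not reliably conservative, and multiple imputation does not by itself correct data missing not at random

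*Protocol article*

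**What the plan says.** Analytical Procedures names three missing-data mechanisms and attaches a method to each.

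- **MCAR:** "For data missing completely at random, single imputation methods can be used to address the missing values". The article describes the consequence in these words: "albeit with a tendency to provide conservative estimates of the treatment effect". The examples given are that "missing values can be replaced with the last observed values or the mean values".
- **MAR and MNAR together:** "For data missing at random and missing not at random, multiple imputation can be used, which produces a more accurate and less biased estimate".

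The section names no other missing-data method. The next paragraph commits to mixed-effects models for continuous outcomes, logistic models for binary outcomes and negative binomial models for counts.

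Three places bear on why data will be missing:

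- Participant Retention: "barriers such as unstable housing and frequent transitions have made it difficult for youth to maintain a consistent mode of communication".
- Analytical Procedures: participants "could discontinue their involvement owing to health issues or fatigue arising from repeated assessments".
- Outcome Areas and Measures, on missed appointments: "This may be even more pronounced in the TAU group that has no interaction with the intervention".

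The sample size allows for 25% attrition. Participant Retention aims to keep about 75% of participants and cites retention of 65% to 85% in earlier research.

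**The concern.** The article asserts statistical properties that the methods lack.

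1. Under MCAR the observed data already give unbiased estimates, so single imputation solves no problem. Whether it is conservative depends on which mean is used and, for last-value filling, on time trends and the pattern of loss.
2. Standard multiple imputation draws missing values from a model fitted to observed data, which is the MAR assumption. It addresses MNAR only if the analyst adds an explicit statement of how unobserved values differ. The article adds none, yet promises less bias.
3. MCAR can be contradicted by the data but never established, and MAR and MNAR cannot be told apart from observed data. A scheme keyed to the mechanism leaves the choice to judgement after the data are seen.

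Housing and health are primary domains and also appear among the stated reasons for losing contact or stopping. The 24-month analysis is underway and will be reported publicly.

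**Working it through.** The article gives no figure for the effect of missing data, so there is none to reproduce.

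**Inputs from the document:** missing share m = 0.25; effect 0.5 SD; α = 0.05 (two-sided assumed); 44 + 31 = 75 HF and 42 + 31 = 73 TAU, so about 74 per arm. The cited retention of 65% to 85% gives a range for m of 0.15 to 0.35.

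**Step 1. Arm-mean filling under MCAR.** Filled values add no spread, so the sample variance falls to about (1−m)σ², while the analysis counts all N per arm.

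- Reported SE = √[2(1−m)σ²/N] = √(2×0.75/74) = 0.142
- True SE = √[2σ²/((1−m)N)] = √(2/55.5) = 0.190
- Ratio = 1−m = 0.75
- Type I error = 2[1−Φ(1.96×0.75)] = 2[1−Φ(1.47)] = 14.2%
- Range: 9.6% at m = 0.15; 20.3% at m = 0.35

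A simulation (74 per arm, 2,000 trials, assumed baseline-outcome correlation 0.5) gave a mean reported SE of 0.141 against an actual 0.187, and type I error of 13.5%. With a true effect of 0.5 the estimate was 0.501. This method is anti-conservative.

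**Step 2. Overall-mean filling, and last value without a trend, under MCAR.** The expected difference is (1−m)×0.5 = 0.375. The last-value figure assumes the baseline value is carried forward; later carried values could attenuate less. The simulation gave 0.375 and 0.376, with type I error of 4.3% and 4.4%. Here the article's description is right.

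The two kinds of mean therefore give opposite answers, and the article does not say which it intends.

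**Step 3. Multiple imputation by mechanism** (same simulation, 20 imputations; the MNAR rows assume logistic missingness with slope 1 per SD of outcome):

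| Mechanism | Estimate, true 0 | Type I error | Estimate, true 0.5 |
|---|---|---|---|
| MCAR, 25% | 0.00 | 4.8% | 0.501 |
| MAR | 0.00 | 5.0% | 0.503 |
| MNAR, same mechanism in both arms | 0.00 | 4.9% | 0.446 |
| 15% random loss in HF, 35% outcome-dependent in TAU, poor outcomes lost | −0.22 | 22.6% | 0.28 |
| As above, good outcomes lost | +0.22 | 24.6% | 0.72 |

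Multiple imputation works under MCAR and MAR. Under MNAR its bias can be modest or large and can run either way. In the last two rows last-value filling had the smaller bias at a true effect of 0 (about 0.10 against 0.22), so even the comparative claim of less bias is not assured.

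**The case against.** **The wording is permissive.** The methods can be used; the article does not say they will be. The firm commitments are the models in the next paragraph, and a likelihood-based mixed model needs no imputation under MAR. This stands and lowers the severity. It does not remove the point: these are the only missing-data methods named, the mixed-model commitment covers only continuous outcomes, and it too relies on MAR. Housing stability is defined from days housed and number of moves, which may be analysed as counts.

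**Conservative is partly right.** Step 2 confirms it for overall-mean filling and for last value without a trend. The error lies in the general claim.

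**A reader might infer that the trial expects MNAR.** The document does not say so. Weaker TAU attendance is put down to incentive, and arm is observed, so that alone is MAR. Housing is recorded every 3 months, so loss that depends on recorded earlier housing is also MAR. MNAR is plausible because current housing and health may drive loss.

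**A reader might infer that last-value filling will favour HF4Y.** With assumed losses of 35% TAU and 15% HF and a shared 30-point rise in days housed, the spurious benefit is (0.35−0.15)×30 = 6 points. But loss that differs by arm is not MCAR, the only case for which the article offers this method, and none of those inputs is in the document.

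**A reader might quote a fixed bias for multiple imputation.** If completers are at 80 (HF) and 60 (TAU) and dropouts are 20 points lower, with the same losses, the true difference is (0.85×80+0.15×60)−(0.65×60+0.35×40) = 77−53 = 24, against 80−60 = 20 observed. This is a complete-case contrast on assumed inputs. In a re-run with outcome-dependent loss and an assumed SD of 30, the bias fell from about 4 points at zero correlation with earlier housing to 3.1, 2.2 and 1.5 at correlations of 0.5, 0.7 and 0.8. It is illustrative only.

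**Sensitivity analyses are commonly left to an analysis plan.** True, and their absence is not the finding. The finding is what the article asserts.

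**Conclusion.** The point holds as a misstatement of method properties, and should be fixed. Single imputation is unnecessary under MCAR and is not reliably conservative: at 25% missing it either shrinks the effect by about 25% or raises type I error to about 14%, depending on a choice the article leaves open. Those two figures need only MCAR, the planned attrition, equal loss by arm and, for last-value filling, no trend with the baseline value carried. Multiple imputation without a departure assumption does not correct MNAR, and MAR cannot be separated from MNAR using observed data.

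The document does not establish that MNAR will occur, how large any bias would be, or which arm it would favour. The MNAR simulation figures show only that bias in either direction is possible. With permissive wording and a MAR-valid model already planned for continuous outcomes, this does not make the trial's analysis invalid.

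**What to change.** - Delete the single-imputation option, the claim that it is conservative, and the choice of method by assumed mechanism.
- For continuous outcomes, state that the planned mixed model is fitted by likelihood to all observed data.
- For binary and count outcomes, name a MAR-valid analysis, such as multiple imputation by arm using site and earlier housing status.
- Before imputing, recover missed 3-month intervals from the next residential timeline follow-back where it covers them. Table 1, footnote b, says it builds the history between successive interviews.
- Replace the MNAR statement with a delta-adjusted (pattern-mixture) tipping-point sensitivity analysis. Shift imputed values by arm over a stated range and report where the conclusion changes.

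The cost is one paragraph of text and one extra sensitivity analysis, with no new data. The change is best made before the final 48-month analysis and applied to the 24-month analysis where still possible.
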